### Expected outcomes

It is expected that focal therapy with IRE in localized PCa has the potential to improve functional outcomes and the quality of life of PCa patients compared to current radical treatment. In line, it is thought that focal ablation, compared to extended ablation, could better preserve important anatomical structures and consequently have fewer side effects and a higher quality of life score. It is shown that the 2D target images produced during the preplanning procedure by the Nanoknife™ system reflect the IRE ablation zone, and could be used as a template for pathology [14]. Whole mount pathology analysis in prostatectomy specimen, obtained with radical prostatectomy 4 weeks following IRE, showed complete haemorrhage, necrosis and fibrosis in the ablated zone [14, 19]. Therefore, it is expected to find fibrosis on TTMB in the according biopsies of the planned ablated zone. Currently, no long-term oncological outcomes exist on IRE ablation of localized PCa, so it may be difficult to predict long-term outcomes. However, short-term oncological outcomes are promising and the aforementioned study showed on whole mount pathology no residual PCa in the ablated zone of all patients [14, 19–22]. It is thought that mpMRI and CEUS imaging are feasible imaging modalities for the follow-up after focal IRE ablation in localized PCa since both mpMRI and CEUS were found to accurately visualize on a short-term basis IRE ablation effects and possible residual PCa [21–23].

### Study design

In this prospective RCT, patients with unilateral PCa (clinical stage T1c-T2b), confirmed on transrectal ultrasound(TRUS)-guided biopsies, will be offered extensive (30-core) TTMB. If the inclusion criteria are met (see below and Table 1), candidates are randomized into two groups. One group will undergo a focal ablation of the prostate (Group A), the other group will receive an extended hemi ablation (Group B) (Fig. 1). Prior to the procedure, a baseline mpMRI, TRUS and CEUS imaging (if available) will be obtained and standardized questionnaires (International Prostate Symptom Score (IPSS), International Index of Erectile Function (IIEF), Quality of life-questionnaire (EPIC), Visual Analogue Scale (VAS)) and number of pads used will be completed by the patients (Fig. 2). After the focal or extended IRE ablation, follow-up will be performed following a strict schedule up to 5 years (Table 2) using mpMRI, TRUS and CEUS imaging (if available), blood tests (PSA, Creatinine), adverse event reporting with Common Terminology Criteria for Adverse Events (CTCAE) and the use of standardized questionnaires (IPSS, IIEF, EPIC, VAS). Six months following the IRE procedure patients will undergo TTMB to determine ablative effectiveness on pathology and to exclude any residual or ‘new’ disease. In case of any positive biopsies on follow-up TTMB, patients will be offered salvage treatment following the EAU Guidelines on Prostate Cancer [3].

**Table 1 Tab1:** Inclusion and exclusion criteria

Inclusion criteria	Exclusion criteria
1. Histologically confirmed organ-confined unilateral PCa on TTMB (clinical stage T1c-T2b)	1. Bleeding disorder (prothrombin time > 14.5 s., partial thromboplastin time > 34 s.), Platelet Count <140/uL, 2. No ability to stop anticoagulant or antiplatelet therapy
2. Gleason sum score 6 or 7	3. Active (urinary tract) infection 4. History of bladder neck contracture 5. Major concurrent debilitating illness or ASA ≥4 6. Cardiac History
3. PSA <15 ng/mL or PSA >15 ng/mL counselled with caution	7. Inflammatory bowel disease 8. Major rectal surgery 9. Previous radiation to pelvis 10. Prior or concurrent malignancy
4. Life expectancy of >10 years, age ≥18 years	11. Biologic or chemotherapy for PCa 12. Hormonal therapy within last 6 months 13. Any resection or stenting of the prostate 14. Prostate calcification >5 mm

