
At present, no randomized controlled trial (RCT) (grade 2b) on IRE for treatment-naïve PCa has been conducted. Moreover, no long-term evidence is available on functional and oncological outcomes following IRE treatment in PCa. In this RCT (NCT01835977) 200 patients with histologically confirmed (on TTMB), organ-confined and unilateral low- to intermediate-risk (Gleason score 6 or 7) PCa will receive ultrasound-guided IRE. Selected candidates will be randomized to either 1) focal ablation or 2) extended hemiablation of the tumour lesions to assess the differences in side effect profile and efficacy of the treatment and to investigate if an extended ablation zone is necessary to treat undetected satellite lesions adjacent to the index lesion (Fig. 1) [24]. Patients will be evaluated on urinary continence, erectile function and quality of life with the use of standardized questionnaires [25–27]. Oncological efficacy will be determined by TTMP, preceded by mpMRI and CEUS imaging if available and PSA follow up.

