### Population

Two hundred patients (age ≥18 years) diagnosed with histologically confirmed, unilateral organ-confined PCa (clinical score of T1c-T2b) with positive biopsies number on transperineal template-guided prostate biopsies and no evidence of lymph node or distant metastases. Patients should have an expected life expectancy of >10 years and serum PSA <15 ng/mL or PSA >15 ng/mL counselled with caution. Patients known with a cardiac history including arrhythmias, ICD or pacemaker and patients with previous pelvic surgery or radiotherapy or PCa treatment are excluded. For all inclusion and exclusion criteria, see Table 2.

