### Quality and patient safety monitoring

Data will be centrally collected and monitored by the CROES using their Data Management System. During the study independent physicians and the IRB, assessing patient safety and treatment efficacy, will monitor data. Monitoring criteria are objectively described in the protocol approved by the IRB, since IRE ablation of soft tissue is a novel prostate cancer treatment and therefore holds potential risks and side effects that are unknown at this time. A clinical risk analysis associated with the NanoKnife™ device and the procedure is presented in Table 3. In accordance to section 10, subsection 1, of the Wet Medisch-Wetenschappelijk Onderzoek met Mensen (Medical Research Involving Human Subjects Act), the investigator will inform the subjects and the reviewing accredited IRB if anything occurs of which the disadvantages of participation may be significantly greater than was foreseen in the research proposal. The study will be suspended pending further review by the accredited IRB, except insofar as suspension would jeopardise the subjects’ health. The local investigator will inform all participating subjects. Interdepartmental monitoring (IDM) will take place according to the IDM model in the AMC.

**Table 3 Tab3:** A clinical risk analysis associated with the IRE device and procedure

Potential risks of IRE ablation and procedure	Side effect/Adverse event
General Anaesthesia	Aspiration, urinary retention, extended muscle blockage, anaesthetic drug toxicity, pain, coma, death
Electric current of IRE	Cardiac arrhythmias, severe muscle contraction, electrical shock, death
Multiple Prostate Biopsies	Bleeding, infection, pain, urinary retention, pain
IRE needle placement and ablation	Damage to urethra/bowel/bladder/nerve with consequent side effects^a^, bleeding, infection, pain
Insufficient IRE treatment	Residual or recurrent tumour
Insufficient Muscle Blockade	Muscle strains or damage, electrodes displaced, trauma

^a^haematuria, hematoma, infection, abscess formation, fistula, sepsis, death, urinary retention, urinary or faecal incontinence, urethra stricture, erectile dysfunction, necrosis of affected tissue

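### The platelet exclusion in Table 1 is printed in a unit that no realistic candidate can fall below, so that one limb of the bleeding screen does not operate as written

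*Protocol article*

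**What the plan says.** Under Study design, candidates who meet the criteria in the text and Table 1 go on to randomisation. The first exclusion in Table 1 combines two clotting-time limits with a platelet limit. The clotting part reads "Bleeding disorder (prothrombin time > 14.5 s., partial thromboplastin time > 34 s" and the platelet part reads "Platelet Count <140/uL". The next exclusion is "No ability to stop anticoagulant or antiplatelet therapy". The article states no platelet limit, unit or reference range anywhere else.

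Table 3, under Quality and patient safety monitoring, lists bleeding as a risk of the multiple biopsies. It lists bleeding again for needle placement and ablation, in the row that opens with "Damage to urethra/bowel/bladder/nerve with consequent side effects".

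On PSA, inclusion criterion 3 in Table 1 is "PSA <15 ng/mL or PSA >15 ng/mL counselled with caution". The Population section repeats it: "serum PSA <15 ng/mL or PSA >15 ng/mL counselled with caution".

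**The concern.** An exclusion threshold is useful only if some candidates can fall on the wrong side of it. A platelet limit of 140 per single microlitre lies so far below any count a man presenting for elective treatment would have that it can exclude nobody. The likely reading is that a multiplier was left out of the unit.

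After passing this check, participants have up to six electrodes placed through the perineal template and a further template-mapping biopsy at six months. The trial's own risk table names bleeding for both kinds of procedure. The trial runs at several centres with central data management, so a unit copied from Table 1 into an eligibility form would switch off the platelet check at every site that applied it literally. The article does not say whether this has happened.

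The PSA wording is a smaller matter. It leaves one value, exactly 15 ng/mL, without a rule.

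**Working it through.** The plan derives no figure for either criterion, so there is no calculation to reproduce. The check is to apply each criterion as a logical rule over a range of values.

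**Platelets.** Input: the limit of 140 per microlitre from Table 1. Rule as printed: exclude if count < 140. Comparison rule, on the assumption that thousands per microlitre were meant: exclude if count < 140 × 1,000 = 140,000.

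| Count per microlitre | Excluded as printed | Excluded if thousands were meant |
|---|---|---|
| 50 | yes | yes |
| 140 | no | yes |
| 1,000 | no | yes |
| 20,000 | no | yes |
| 50,000 | no | yes |
| 100,000 | no | yes |
| 139,999 | no | yes |
| 140,000 | no | no |
| 150,000 | no | no |
| 400,000 | no | no |

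The two rules disagree for every count from 140 up to 139,999, and their limits differ by 140,000 / 140 = 1,000. The documents give no distribution of platelet counts among candidates, so the number of men in that interval cannot be estimated. That real counts lie far above 140 per microlitre is general knowledge and is used here as an assumption.

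**Rest of the bleeding screen.** The prothrombin limit (14.5 s), the partial thromboplastin limit (34 s) and the drug-related exclusion do not depend on the platelet unit. All three still exclude candidates as written.

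**PSA.** Rule: include if PSA < 15, or if PSA > 15 with the counselling condition. Leaving the counselling aside, the rule is true at 0, 5, 14.99, 15.01, 20, 100 and 1,000 ng/mL and false at 15. There is no upper limit. The figure of 15 serves only to trigger counselling, and the value 15 itself belongs to neither branch.

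**The case against.** The strongest reply on platelets is that this is a slip in a journal article. A urologist would read the number as thousands, the IRB-approved protocol is a separate document that is not shown, and nothing indicates that the slip reached it or any eligibility form. That stands as a limit on the likely harm. It does not make the printed criterion right: the article states a wrong decision threshold in a safety exclusion, which is different from leaving out detail. A multiplier lost in typesetting or text conversion is possible but unlikely, since superscripts survive elsewhere, for example in the ablation volume under Fig. 3 and the footnote mark in Table 3.

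Two stronger readings are tempting and are not supported.

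- A reader might infer that bleeding risk goes unscreened. It does not. The clotting-time and anticoagulant or antiplatelet exclusions in the same table remain in force.
- A reader might infer that the PSA criterion is a failed risk limit that lets in men outside the stated population. The documents do not show this. The criterion expressly admits men above 15 ng/mL subject to counselling, and it does so in matching words in Table 1 and in Population, so it is a deliberate soft threshold. The risk label is tied to Gleason score, as in "unilateral low- to intermediate-risk (Gleason score 6 or 7) PCa", and no PSA bound for it is given. The limits "Gleason sum score 6 or 7", stage T1c-T2b and unilateral organ-confined disease all still apply. Whether PSA should be capped is a clinical decision for the investigators.

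**Conclusion.** The platelet limb of the bleeding exclusion is wrong as printed and excludes no realistic candidate. This conclusion needs only the assumption that real counts are far above 140 per microlitre. The factor of 1,000 rests on a further inference, that the unit should be thousands per microlitre, which nothing in the article confirms.

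The consequence is confined to one of several bleeding-related exclusions. It touches no sample size, power or error rate. It still merits correction, because it is the only platelet limit in the document and part of the eligibility rules for an invasive procedure.

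On PSA, all that remains is a small wording gap at exactly 15 ng/mL in a criterion that otherwise does what it says.

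**What to change.** 1. Look up the platelet threshold and its unit in the IRB-approved protocol and correct Table 1 to match. This review does not say what the threshold should be.
2. Confirm that the eligibility form, on paper or in the data management system, carries the correct unit. If it carried the printed one, check the platelet counts of men already enrolled against the approved limit.
3. State which PSA branch covers exactly 15 ng/mL.
4. In the same pass, correct the cross-reference in Population. It sends readers to Table 2 for the eligibility criteria, but Table 2 is the follow-up scheme and the criteria are in Table 1.

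The cost is a short correction to the article and one check of the form. The design, analysis and recruitment target are unchanged.

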**Fig. 2 Fig2:**
[figure not shown]
Flowchart of the inclusion and randomization process

**Table 2 Tab2:** Overview follow-up scheme

Visits	Day −1	Day 0; IRE	Day 1	2 weeks	4 weeks	3 months	6 months	1 year	18 months	2 years	30 months	3,4,5 years
Medical History	X											
Phys. Examination	X			X	X	X	X	X	X	X	X	X
Informed Consent	X											
PSA/Creatinine test	X			X	X	X	X	X	X	X	X	X
Questionnaires (IIEF,IPSS,EPIC,pads)	X				X	X	X	X	X	X	X	X
Pain-scores (VAS)	X		X	X	X	X	X	X	X	X	X	X
(mp)MRI and if available CEUS	X						X	X		X		X
TTMB	X						X					
IRE procedure		X										
AEs reporting		X	X	X	X	X	X	X	X	X	X	X

### Population

Two hundred patients (age ≥18 years) diagnosed with histologically confirmed, unilateral organ-confined PCa (clinical score of T1c-T2b) with positive biopsies number on transperineal template-guided prostate biopsies and no evidence of lymph node or distant metastases. Patients should have an expected life expectancy of >10 years and serum PSA <15 ng/mL or PSA >15 ng/mL counselled with caution. Patients known with a cardiac history including arrhythmias, ICD or pacemaker and patients with previous pelvic surgery or radiotherapy or PCa treatment are excluded. For all inclusion and exclusion criteria, see Table 2.

### Study procedures

#### Transperineal template-mapping biopsies

Extensive transperineal three-dimensional (3D)-template mapping biopsies are performed using ultrasound guidance to localize cancer foci by applying the same transperineal grid used for brachytherapy seed placement. This is considered to be the reference standard for patient selection in focal therapy for localized PCa [28]. TRUS biopsy, even with optimized protocols, has been shown to poorly reflect the tumour grade and extent of PCa compared with radical prostatectomy specimens [29, 30]. Needle biopsies will be analysed on diagnosis/residual/recurrent PCa and tumour grade by a specialized uro-pathologist.

#### IRE ablation

The AngioDynamics Inc. HVP-01 Electroporation System (also registered as the NanoKnife™ IRE System) is the first commercially available device based on IRE and is used for tissue ablation that is primarily cellular [13]. It is approved by the regulatory authorities in Europe (CE certificate) and meets several international recognized standards. The NanoKnife™ System and Probes have been cleared for marketing by the U.S. Food and Drug Administration (FDA) via 510(k) Premarket Notifications (K060054, K080202, K080376, and K080287). The console consists of two major components; a Low Energy Direct Current generator and needle electrodes.

Prior to the procedure patients will receive antibiotic prophylaxis (Ciprofloxacin 500 mg). A maximum of six IRE electrodes will be placed using a brachytherapy template-grid into the pre-specified ablation zone using biplane transrectal ultrasound image guidance to visualize both sagittal and axial views. The ultrasound data on prostate dimensions, electrode position and electrode tip length are transferred into the software platform and the resultant ablation volume will be determined and displayed by the Nanoknife™ console (Fig. 3). When the needles are in place, 90 consecutive pulses will be delivered of high-voltage (1500 V/cm) with a direct current between 20 and 50 A. Pulses are delivered (synchronized with ECG) in groups of 10 at intervals of 100 μs. Between each group, a 3.5 s delay is required to recharge the capacitor. During the IRE procedure patients will receive a strong muscle relaxant (Rocuronium) to prevent severe muscle contraction. The total procedure time, including general anaesthesia, will be approximately 1 h. After the procedure patient will receive a transurethral catheter for 24 h. Patients will have an overnight hospital stay and it is anticipated that the majority of patients will be discharged the day after the procedure. Procedural and post procedure Adverse Events (AEs) and Serious AEs will be reported to the Institutional Review Board (IRB).

**Fig. 3 Fig3:**
[figure not shown]
**a** The Nanoknife console. **b** Specific ablation zone: with the needles placed 1.5 cm apart, the active electrode length is set at 2 cm and the resultant ablation volume is calculated at 12.75 cm^3^

#### Multiparametric magnetic resonance imaging

mpMRI will be performed in supine position on a 1.5 T AVANTO® MRI scanner (Siemens Healthcare, Erlangen, Germany) using an integrated endorectal-pelvic phased-array coil (Medrad, Warrendale, USA). Prior to the mpMRI, anti-Peristaltic Drugs (Buscopan or Glucagon) will be given. T2 weighted sequences will be performed in sagittal, coronal and transverse planes from the aorta bifurcation to the pubic symphysis, including prostate and seminal vesicles. Next, T1 diffusion-weighted with fat suppression and dynamic contrast-enhanced images (0.1 mmol of gadopentetate dimeglumine per kg of body weight, Gadolinium DTPA, Gadovist) are obtained. mpMRI will be evaluated by a specialized uro-radiologist (blinded for the randomization) on prostate and ablation volume, evidence of residual or recurrent PCa according to the PIRADS (v2) criteria [31], skip lesions within the target zone, damage to adjacent structures and lymph node or haematogenous metastasis.

#### Contrast-enhanced ultrasound

CEUS imaging involves the use of microbubble contrast agent (SonoVue; Bracco, Milan, Italy) to show blood flow and tissue perfusion information. The ultrasound contrast agent consists of a solution of gas-filled shell-stabilized microbubbles with a diameter of 3–5 μm. These bubbles stay inside the blood stream and travel through all blood vessels, including the microvasculature [32] and are visualized with specialised imaging techniques (Philips iU22; Philips Healthcare, Bothell, USA). The prostate will be scanned in 4 planes, base, mid-base, mid-apex and apex. If performed, CEUS imaging will be analysed on prostate and ablation volume and evidence of residual or recurrent PCa by the performing urologist/fellow.

### Randomization, sample size and statistical analysis

#### Randomization

The patients are stratified on baseline total IIEF-score with cut-off score of 45 points (≤45 vs. >45), Gleason score (grouped in Gleason sum score 6 vs. sum score 7) and age with cut-off score of 60 years (≤60 and >60) to prevent randomly occurring differences in important prognostic factors across the two randomized groups. Patients are blinded to the randomized treatment given (focal or extended ablation) to ensure unbiased assessment. The treating physicians have to be informed about the actual treatment in order to be able to perform the ablation. mpMRI findings will be coded and centrally assessed by a uro-radiologist, blinded for the results of TTMB and the performed procedure.

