#### Sample size calculation

Since the primary objective of the study is to determine the side effect profile of IRE, the sample size is powered on a common event; erectile dysfunction. *Ahmed* et al. performed three comparable studies with a concurrent focal ablation modality (HIFU), and a similar patient population and the same primary objectives [33–35]. Focal ablation with HIFU led to a decline of 18.2 % on the IIEF-15 questionnaire (57.5 % to 47.0 % after 12 months). Converting this to the shortened IIEF-5 questionnaire (which is used in this RCT), the mean IIEF score is 16.61 (SD 4.0) in Group A (focal ablation) and the mean IIEF score is 15.1 (SD 4.0) in Group B (extended ablation). A two group Wells-Satterthwaite *t*-test of equal means and unequal variances were used to calculate the sample size. The one-sided (one-tailed) test was used, because this rejects the null hypothesis for differences in a single direction. With an α level of 0.05 and power of 80 % (1-β), the sample size required was at least 90 men per group. The sample size was adjusted to allow for 35 % of men in the general population (>50 years old) having poor baseline erectile function [36], and therefore aim to recruit at least 200 men in total.

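### The stratification cut-off of 45 on the total IIEF is incompatible with the IIEF-5, the instrument that the protocol says it uses

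*Protocol article*

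**What the plan says.** The Randomization section of the protocol article sets three two-level factors. The first reads "The patients are stratified on baseline total IIEF-score with cut-off score of 45 points", which splits men into those scoring up to 45 and those scoring higher. The remaining factors are "Gleason score (grouped in Gleason sum score 6 vs. sum score 7) and age with cut-off score of 60 years". The stated purpose is "to prevent randomly occurring differences in important prognostic factors across the two randomized groups".

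The next section, Sample size calculation, powers the trial on erectile dysfunction. It starts from earlier HIFU studies: "Focal ablation with HIFU led to a decline of 18.2 % on the IIEF-15 questionnaire (57.5 % to 47.0 % after 12 months". It then changes scale: "Converting this to the shortened IIEF-5 questionnaire (which is used in this RCT"). For the focal arm, the planning value on the shorter scale is "the mean IIEF score is 16.61 (SD 4.0) in Group A (focal ablation"). The extended arm is given a mean of 15.1 with the same SD.

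Elsewhere (Study objectives, Study design, the follow-up scheme in Table 2, Abbreviations) the article says only IIEF, without a version. In Table 2 a single questionnaire row covers the baseline visit and follow-up.

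**The concern.** Two adjacent sections make statements that cannot both hold for one questionnaire. A total of 45 suits the 15-item form. It cannot occur on a five-item form whose planning means are about 15 to 17.

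This is not a detail left to a fuller document, because the article states both the cut-off and the instrument. What is at stake depends on which statement is wrong:

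- **The IIEF-5 is the baseline form.** The cut-off separates nobody, and baseline erectile function is left to chance. It is one of three factors that the protocol calls important, and it is the baseline level of the outcome on which the trial is sized.
- **The 15-item form is collected.** The stratification works, but the instrument named for the powered outcome is wrong or incompletely described. The reader cannot tell on which scale the difference of 1.51 points will be tested.

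**Working it through.** **1. The plan's own sample size.** Inputs from Sample size calculation: means 16.61 and 15.1, so δ = 1.51; SD 4.0; one-sided α 0.05; power 80%.

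- Normal approximation: n = 2(1.645 + 0.842)² × 4.0² / 1.51² ≈ 86.8, so 87 per group.
- One-sided two-sample t-test: 87.45, so 88 per group.
- Power at 90 per group: 81.0%.

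The stated minimum of 90 per group is reproduced to within a few men. The sample size was therefore worked out on the IIEF-5 scale.

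**2. Where 45 lies on that scale.**

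- From the Group A planning mean: (45 − 16.61)/4.0 = 7.1 SD.
- From the Group B planning mean: (45 − 15.1)/4.0 = 7.5 SD.
- With a normal distribution at the Group A mean, the expected number above 45 among 200 men is about 1 × 10⁻¹⁰.

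These are planned post-treatment means, and baseline should be higher. The article gives no baseline IIEF-5 mean, so two rough values are assumed:

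- 57.5/3 = 19.2 (reading the HIFU figures as points, although they are printed with percent signs): (45 − 19.2)/4.0 ≈ 6.5 SD.
- 16.61/(1 − 0.182) = 20.3: (45 − 20.3)/4.0 ≈ 6.2 SD.

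The maximum of 5 × 5 = 25 comes from the instrument's definition and is not printed in the article. The article's own means and SD give the same answer without it.

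**3. Effect on the strata.** As intended: 2 (IIEF) × 2 (Gleason) × 2 (age) = 8. If the IIEF-5 is the baseline form: 1 × 2 × 2 = 4.

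**4. Size of the lost protection.** Assumptions: normal baseline IIEF-5, SD 4 (set equal to the planning SD), 100 men per group (200/2), and ideal balance on any working factor.

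- No working factor: 1.96 × 4 × √(2/100) = ±1.11 points.
- Cut at the mean: a fraction 1 − 2/π = 0.36 of the variance remains within strata, so 1.11 × √0.36 ≈ ±0.67.
- Cut at 15 with an assumed mean of 19.2: z = (15 − 19.2)/4 ≈ −1.04, with a share below of p ≈ 0.149 and a normal density of 0.232. The fraction remaining is 1 − 0.232²/(0.149 × 0.851) ≈ 0.58, so 1.11 × √0.58 ≈ ±0.84.

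The loss at the 95% limit is 1.11 − 0.84 ≈ 0.3 to 1.11 − 0.67 ≈ 0.4 points.

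**5. The origin of 45.** Read as points, the HIFU values of 57.5 and 47.0 on the IIEF-15 lie close to 45. This suggests, but does not show, that the cut-off was set on the longer form.

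**The case against.** The best defence is that the baseline total IIEF score means the 15-item total, with the IIEF-5 derived from it for the outcome. The value 45 fits that reading, and the only text placing the IIEF-5 in the trial is a parenthesis within the sample-size conversion. This stands as a possibility. A reader might infer as fact that all 200 men fall on one side of the cut, but the article does not support that without condition, because it depends on the parenthesis being right about the baseline form. The defence does not remove the inconsistency, since nowhere does the article say that the 15-item form is given or that the IIEF-5 is derived from it.

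A second defence concerns the consequence, and it largely stands. Randomisation without this factor is still unbiased, Gleason score and age still stratify, and the standard error already allows for chance imbalance. The article also calls the group analyses hypothesis-generating. A reader might set ±1.1 points against the target of 1.51 and take that as the damage. That would be too strong for two reasons. A working two-level factor would still leave ±0.7 to ±0.8. And baseline imbalance passes in full to the outcome only if the slope of outcome on baseline is 1.

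Nor does the text rank baseline IIEF as the strongest prognostic factor; it lists three factors as important.

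**Conclusion.** The point holds as an internal inconsistency that should be fixed: a cut-off of 45 cannot be applied to the instrument that the article says it uses. That conclusion rests on the article's own planning values and survives any plausible baseline mean.

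The consequence is conditional. With the IIEF-5 at baseline, the IIEF factor does nothing and eight strata become four. With the 15-item form, the factor works and the description of the powered outcome needs correcting.

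In the first case the cost is modest: the 95% range of chance imbalance is about ±1.1 points instead of about ±0.7 to ±0.8, under the assumptions in step 4. Neither the validity of the allocation nor the arithmetic of the 90 men per group is affected.

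**What to change.** - Name the IIEF version given at baseline and the version analysed as the outcome.
- If only the IIEF-5 is given, replace 45 with a justified value within its range. Proportional rescaling gives 45/75 × 25 = 15 (75 being the 15-item maximum at 5 points per item), but this is only an illustration. The article's own conversion does not follow simple thirds, since 47.0/3 = 15.7 matches neither 16.61 nor 15.1.
- If the 15-item form is given, keep 45. Then either state that the IIEF-5 is derived from that form, or correct the statement that the IIEF-5 is used and express the powered outcome on the collected scale.
- Check which scale and cut-off are set in the randomisation system.
- In either case, adjust the between-group analysis for continuous baseline IIEF. The score is already collected, and the adjustment also covers men already randomised.

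The cost is a wording correction, at most one parameter in the randomisation system, and one covariate in the analysis. No further data or patients are needed. A changed cut-off helps only men randomised after the change, so the check should be made early.
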